### Twelve subjects will receive the vaccine, 6 in the groin area, subcutaneously (SQ) and 6 in the deltoid region intramuscularly (IM). Six subjects will receive placebo, 3 in the groin SQ and 3 in the deltoid region IM. The table shows two sets of probabilities for observing adverse events. *Visit-specific* probabilities refer to adverse events that have a common, independent rate of occurrence for each of the four vaccination visits, i.e. the relevant n is the total number of injections. *Patient-specific* probabilities refer to adverse events that affect a given proportion of subjects, i.e. the relevant n is the number of patients. The first pair of columns give probabilities of observing one or more and two or more adverse events in a particular 6 patient arm. The next pair of columns gives probabilities for observing events in the 12 patient treatment group as a whole. The final pair of columns gives these probabilities for all 18 patients in the trial.

### If a given toxicity affects 5% of patients in the treatment groups, then the probability that one or more events are observed among the 12 subjects is 46% (91% if this event rate is visit-specific). If the toxicity occurs at this same 5% rate but in only one of the 6 patient arms (e.g. deltoid treatment), the corresponding probabilities of observing one or more events are 26% and 71%. There is 80% probability to detect one or more occurrences of an event with a patient-specific (visit-specific) rate of 24% (6.5%) with 6 subjects or a 13% (3.3%) event rate with 12 subjects (not shown in table).

| **Event Rate** | | **Probability of AE’s in a 6 patient arm of the trial** | | **Probablity of AE’s in 12 patient treatment group** | | **Probability of AE’s in entire patient group** | |
| --- | --- | --- | --- | --- | --- | --- | --- |
| **Pr{1 or more events }** | **Pr{2 or more events }** | **Pr{1 or more events }** | **Pr{2 or more events }** | **Pr{1 or more events }** | **Pr{2 or more events }** |
| Patient-specific adverse event rate | 1% | 0.059 | 0.001 | 0.114 | 0.006 | 0.165 | 0.014 |
| 5% | 0.265 | 0.033 | 0.460 | 0.118 | 0.603 | 0.226 |
| 10% | 0.469 | 0.114 | 0.718 | 0.341 | 0.850 | 0.550 |
| 20% | 0.738 | 0.345 | 0.931 | 0.725 | 0.982 | 0.901 |
| 30% | 0.882 | 0.580 | 0.986 | 0.915 | 0.998 | 0.986 |
| 40% | 0.953 | 0.767 | 0.998 | 0.980 | 0.999 | 0.999 |
| 50% | 0.984 | 0.891 | 0.999 | 0.997 | 0.999 | 0.999 |
| Visit-specific adverse event rate | 1% | 0.214 | 0.024 | 0.383 | 0.083 | 0.515 | 0.162 |
| 5% | 0.708 | 0.339 | 0.915 | 0.699 | 0.975 | 0.881 |
| 10% | 0.920 | 0.708 | 0.994 | 0.960 | 0.999 | 0.995 |
| 20% | 0.995 | 0.967 | 1.000 | 1.000 | 1.000 | 1.000 |
| 30% | 1.000 | 0.998 | 1.000 | 1.000 | 1.000 | 1.000 |
| 40% | 1.000 | 1.000 | 1.000 | 1.000 | 1.000 | 1.000 |
| 50% | 1.000 | 1.000 | 1.000 | 1.000 | 1.000 | 1.000 |

**7.0 RANDOMIZATION AND BLINDING**

This is a randomized, modified double-blind placebo-controlled study. The 18 subjects in the study will be randomized first into either the deltoid or groin group, then to the treatment or placebo arm. The randomization plan is based on three groups of six patients each so that within each sequential cohort of 6 recruited subjects, three will randomly be assigned to groin and the other three will receive deltoid immunization. Each of these subgroups will also be randomized so that two subjects will receive active treatment whereas the other will receive placebo. This approach was felt necessary to achieve a balanced design, even if the study does not recruit all planned subjects.

The vaccine and placebo have a slightly different appearance. In order to maintain the modified blind a trained RN or Nurse Practitioner will deliver the vaccine or placebo not otherwise associated with the study. The study staff will handle all processes relating to subject study participation, care and monitoring except for actual vaccination. Staff will remain in the immediate vicinity of the subject during vaccination.

- 1. **HUMAN SUBJECTS**

Each subject must be a human immunodeficiency virus type 1 (HIV-1) seronegative man or non-pregnant woman with a low risk profile for HIV-1, and at least 18 years old.

- 1. **Inclusion Criteria**

1. Age: 18 – 60 years of age.
2. Female or male (for females, negative serum pregnancy test at time of entry into the study and assurance of adequate, reliable birth control measures until at least 60 days after the final immunization or documentation of non-reproductive status e.g. record of tubal ligation).
3. At low risk for acquiring HIV-1 (no STD within one year of beginning trial, no history of injection drug use, no sex with an HIV infected individual or active injection drug user within six months of beginning trial, no unsafe sexual activity with unknown partners or mutually monogamous relationship with a known HIV seronegative partner (per subject report) for the last six months.
4. Normal history and physical examination.
5. Normal complete blood count, differential, ALT and creatnine.
6. Negative for HIV by an FDA approved blood test, negative hepatitis B surface antigen and anti-HCV or negative HCV PCR if anti-HCV positive.
7. Capable of giving informed consent.
8. Willing to abstain from receptive anal intercourse during the 14 months of the study
9. Available for follow-up during the 14 month duration of the study.
   1. **Exclusion Criteria**
10. Pregnant or lactating women.
11. Allergy to eggs or neomycin
12. Vaccination with live attenuated vaccines within 60 days of study [medically indicated subunit or killed vaccines (e.g., influenza, pneumococcal) are not exclusionary, but should be given at least one month prior to first immunization, and not until 14 days following the last immunization.
13. Significant gastrointestinal complaints such as inflammatory bowel disease or chronic diarrhea.
14. Immunosuppression of any type including those related to lupus, rheumatoid arthritis, leukemia, lymphoma, generalized malignancy, agammaglobulinemia, therapy with alkylating agents, antimetabolites, or radiation.
15. Recent (past 6 months) or current use of immunosuppressive medications; i.e. oral, parenteral and orally inhaled corticosteroids, and/or cytotoxic medications.
16. Thyroid disease including history of thyroidectomy and diagnoses requiring medication
17. Unstable asthma, exposure to or active tuberculosis, seizure disorders, bleeding disorders, splenectomy, hypertension (less than 150/100 if on medication).
18. Medical or psychiatric condition or occupational responsibilities that preclude subject compliance with the protocol. Specifically excluded are persons with a history of suicide attempts, recent suicidal ideation or who have past or present psychosis.
19. Prior receipt of HIV-1 vaccines or placebo in previous HIV vaccine trial
20. Receipt of blood products 120 days prior to HIV screening
21. Receipt of immunoglobulins 60 days prior to HIV screening
22. Any history of anaphylaxis or history of other serious adverse reactions to vaccines.
23. History of serious allergic reaction to any substance requiring hospitalization or emergent medical care (e.g., Stevens-Johnson syndrome, bronchospasm, or hypotension).
24. History of non-prescribed injection drug use.
25. Use of experimental agents within 30 days prior to study.
    1. **Benefit of Participation**

This study is not thought to be of direct benefit to the subject. The possible benefit to humanity and the scientific community includes a better understanding of the human immune system and resistance to HIV infection, which may lead to improved treatments and/or vaccines against HIV infection.

To defray expenses and compensate participants for their time, they will be paid for participation in this study. Each participant will be paid $25 for each blood donation or clinical exam visit, $200 for immunization visits which may include a blood donation and $100 for the flexible sigmoidoscopy with mucosal biopsy visits which may include a blood donation. Participants will be paid in cash at each visit. All subjects who have positive HIV-1 serology at the end of the study as measured by an FDA-approved HIV-1, 2 ELISA and/or Western Blot kit, will be offered follow-up HIV-1 diagnostic testing by HIV-1 RNA PCR through the [name] Lab after the completion of the study. In addition, the participants will be given $750 to cover the approximate clinical cost of three PCR tests when the participant or his/her healthcare provider feels it is indicated. This is based on the current average cost of $250 per test. Participants will also be provided with transportation, if needed, or parking at the clinical site on the day of any procedure.

**8.4 Withdrawal from study**

**8.4.1 Subject-initiated withdrawal**

If any participant should choose to withdraw from the study, they will be informed through the consent that it will not affect their relationship with UCLA Medical Center, or their right to health care or other services to which they are otherwise entitled. Additionally, if a volunteer decides not to participate, he or she is free to withdraw consent and discontinue participation at any time without prejudice to future care at UCLA.

**8.4.2 Investigator-initiated withdrawal**

The investigator may withdraw a subject from participating in this research if circumstances arise which warrant doing so. The investigator, [name], will make the decision and inform participants of these circumstances. This decision may be made either to protect participants’ health and safety, because a condition develops that places the participant in an exclusion category or because baseline responses will not permit an effective comparison with post-immunization results.

Experiences of grade 4 (potentially life threatening) will automatically exclude subjects from further participation in the trial. [name] and [name] will evaluate all SAEs and grade three (severe) experiences to determine if the episode represents an ongoing risk related to the study and make a determination about the subject’s further participation in the study. Grade 1 and 2 experiences will generally not be exclusionary unless they are related to the immunization and progressive in degree or persistent.

The decision to withdraw a participant may be made in the case of:

- Grade 4 adverse experiences
- Grade 3 adverse experiences related to the immunization and a determination that the duration or other factor indicates withdrawal is in the best interest of the subject
- Serious Adverse Experiences regardless of grade of individual event
- Grade 1 and 2 experiences related to the immunizations that are progressive in degree or persistent.
- HIV-1 infection
- Pregnancy

**8.4.3 Withdrawal Due to HIV-1 Infection**

If tests indicate that the subject is infected with HIV, either the subject or their primary health care provider will be notified (depending upon which method the subject has selected on the consent form). If the subject will be informed directly, a research staff member who is trained and experienced in counseling individuals in this area will work with the subject. The subjects will be offered referrals to assist with any emotional, medical, or other support needs they may have relating to HIV infection.

**9.0 IMMUNIZATION PROCEDURES**

- 1. **ALVAC-HIV (vCP205)**
     1. **Preparation of Dosing Solution:**

Aventis Pasteur ALVAC-HIV (vCP205) lot # S3673 at a 1x 106.87 TCID50 will be used. Prior to injection, each dose of vaccine is reconstituted by dissolution of the lyophilisate with the diluent supplied, i.e., sterile saline solution NaCl 0.4%. The diluent will be injected slowly into the vial containing the lyophilized ALVAC. Then, the vial will be swirled gently until dissolution of the lyophilisate. Avoid inverting the vial. The reconstituted vaccine must be kept at 2-8°C and used within two hours. Do not freeze.

**ALVAC Placebo** is supplied as a sterile, lyophilized product that consists of a mixture of virus stabilizer, and freeze drying medium. The diluent supplied for reconstitution of ALVAC-Placebo consists of sterile 0.4% NaCl and conforms to established requirements for sterility, safety, and pyrogen testing. The volume of the prepared vaccine is 1 mL.

- - 1. **Administration of ALVAC-HIV (vCP205)**

The vaccine will be prepared by the UCLA Research Pharmacy within two hours of administration to the subject. The vaccine or placebo is preassigned to the subject’s study ID number. The preparing pharmacist and a second pharmacist will note the subject study ID number, dose and vaccine or placebo in the dispensation log and on the label of the syringe. In order to maintain blinding, the vaccination will be administered by a trained Registered Nurse, Nurse Practitioner, Physician or similar licensed staff not otherwise involved with the safety and monitoring of the subjects. The person administering the vaccine or placebo will also document the date and drug randomization, as noted on the label of the syringe, in a separate log that will be kept in the General Clinical Research Center.

Immunization. All four immunizations with ALVAC-HIV (vCP205) will utilize the same dilution.

Clean the skin with alcohol

- Draw 1 ml of the vaccine into a syringe for standard subcutaneous (groin) or intramuscular (deltoid) injection.
- Using a 25g 5/8” needle, administer the injections subcutaneously into the groin area avoiding femoral arteries and nerve pathways. Groin injections will be placed unilaterally, medial to the femoral artery, vein and nerve (approximately halfway between the anterior superior iliac spine and the symphysis pubis) and anterior to the horizontal group of superficial inguinal lymph nodes. Immunization site will be unilateral groin delivery. Immunizations #1 and #3 will be administered to the subjects’ right side and immunizations #2 and #4 will be administered to their left.

-or-

- Using a 21g 1” needle, administer the injections intramuscularly into the deltoid region. Deltoid injections will be placed in the midlateral aspect of the deltoid muscle, 5-8 cm inferior to the scapular acromion process and the lateral edge of the clavicle. Immunization site will be unilateral deltoid delivery. Immunizations #1 and #3 will be administered to the subjects’ right side and immunizations #2 and #4 will be administered to their left.
  - 1. **Route of Immunization**

The vaccine or placebo will be administered subcutaneously (1 ml) unilaterally to inguinal region (alternating sides each sequential immunization), medial to the femoral artery, vein and nerve or IM (1 ml) unilaterally to deltoid region (alternating sides each sequential immunization)

- 1. Vaccine Administration Schedule

| Route/Volume of ALVAC-HIV (vCP205) or placebo | IMMUNIZATIONS | | | |
| --- | --- | --- | --- | --- |
|  | 1 (day 0) | 2 (day 7) | 3 (day 14) | 4(day 21) |
| Subcutaneous  or  Intramuscular  1 ml | ALVAC-HIV (vCP205) | ALVAC-HIV (vCP205) | ALVAC-HIV (vCP205) | ALVAC-HIV (vCP205) |
| placebo | placebo | placebo | placebo |

- 1. **Disposal**

Partially-used and empty vials will be destroyed on site after final vaccine accountability is performed by crushing or incineration according to UCLA Environmental Health and Safety biohazard procedures. All expired or unused vaccine vials will be returned to Aventis Pasteur S.A. Study supplies, including partially used vials, will not be administered to other subjects or used for *in vitro* or animal experiments. All used syringes and needles will be placed into a biohazard “sharps” container and disposed of following the designated UCLA procedures for disposal of potentially infectious materials. Disposal of all materials will be done in accordance with UCLA “Safety Procedures-Standard Operating Procedures”.

1. **IMMUNOLOGIC AND VIROLOGIC STUDIES TO BE PERFORMED**
   1. **Safety**

Assessment of product safety will include extensive monitoring of physical, hematologic, chemistry and immunologic parameters, as well as subjects’ self-report of symptoms/responses.

- 1. **Plan for Evaluation of Immune Responses**

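### The syringe label names the assignment, and nothing described hides it from the subject or the nearby monitoring staff: an avoidable risk to the blind at each injection

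*Protocol*

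**What the plan says.** Section 7.0 declares the design: "This is a randomized, modified double-blind placebo-controlled study". It gives the reason for the qualifier: "The vaccine and placebo have a slightly different appearance". The injection is therefore given by a nurse who has no other part in the study. On everyone else, section 7.0 says: "The study staff will handle all processes relating to subject study participation, care and monitoring except for actual vaccination". It then adds: "Staff will remain in the immediate vicinity of the subject during vaccination".

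Section 9.1 (Administration) states that product is assigned in advance to each study ID. Two pharmacists "will note the subject study ID number, dose and vaccine or placebo in the dispensation log and on the label of the syringe". The injector is to be a nurse, physician or "similar licensed staff not otherwise involved with the safety and monitoring of the subjects". That person "will also document the date and drug randomization, as noted on the label of the syringe, in a separate log", which is held in the General Clinical Research Center. No restriction on access to that log is stated.

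**The concern.** The blind rests on separating the person who injects from the people who assess. The labelling rule works against this, because it puts the assignment in plain words on an object used in front of the subject while the assessors stand near.

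Safety is the primary objective (section 1.1), and part of the safety evidence is open to expectation. Subjects record local reactions on a diary card, and study staff examine them in person three days after each injection (section 4.1). The monitored list in section 5.1 includes pain, tenderness, muscle ache, headache, nausea and fatigue. Under section 8.4.2, decisions on whether a subject continues after grade 1 to 3 events turn partly on whether the event is judged related to the immunization. A subject or assessor who knows the assignment may report, grade or attribute such events differently. Route is plain to everyone at the bedside, so vaccine versus placebo is the only contrast that can be masked there.

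**Working it through.** The plan gives no figure on this point, so there is none to reproduce. The check sets sections 7.0 and 9.1 side by side and then counts the exposures.

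**1. Does the label show the true assignment?** Yes. Section 9.1 puts vaccine or placebo on it. A coded label is ruled out by the next step, in which the injector must "document the date and drug randomization, as noted on the label of the syringe". That can be done only if the label is readable as an assignment.

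**2. Who could see it, and what prevents that?**

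| Person | Needs to be blind? | Safeguard described | Label or contents hidden? |
| --- | --- | --- | --- |
| Pharmacists | No | Separate role | Not needed |
| Injector | No, under the modified blind | Separate role | Not needed |
| Subject | Yes | None described | No |
| Monitoring staff | Yes | Do not give the injection | No; they stay close by |

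The safeguard covers who handles the syringe. It does not cover who can look at it.

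**3. Does the label need the assignment to reach the right subject?** No. Product is already tied to the study ID, and the dispensation log holds the assignment. The label's one further use is as the source for the injector's log.

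**4. How many exposures?**
- Inputs: 12 vaccine and 6 placebo subjects (section 6.1); injections on days 0, 7, 14 and 21 (Protocol Summary and section 10.2.1).
- Vaccine syringes: 12 × 4 = 48. Placebo syringes: 6 × 4 = 24. Total: 18 × 4 = 72.
- The Protocol Summary asks for 18 subjects completing to day 24 and allows up to 24 to sign consent. If all 24 were dosed four times, the count would be 24 × 4 = 96. That is a ceiling, since some would withdraw before or during dosing. If recruitment falls short, which section 7.0 allows for, the count falls below 72.
- A subject keeps the same assignment for all four doses, so one sighting on any of four occasions is enough.

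**5. Which data are affected?** Most open: diary entries, symptom reports, severity grades and relatedness. Less open: blood counts, ALT, creatinine and CD4/CD8 counts.

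**The case against.** The strongest reply is that the protocol nowhere says that a subject or a monitor reads a label. Being near the subject is not the same as being within reading distance of a small syringe label. The modified blind is declared openly, and an unblinded injector is part of it. This stands: the documents show an opening, not a breach, and they give no basis for estimating how often a sighting would occur.

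A second reply is that the label serves a purpose. It is the source for a bedside record of what was given, and removing the assignment gives that up. This also stands, and the fix has to allow for it.

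Three stronger readings are tempting, and the documents do not support them:

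- **That the primary analysis is a biased comparison with placebo.** Section 1.1 sets out to evaluate safety at the two sites and names no vaccine-placebo contrast; placebo enters as a comparator in the secondary objective (section 1.2). The calculations in section 6.1 give chances of observing events in 6, 12 or 18 subjects and compare no arms. What is at risk is the quality of reporting, grading and attribution.
- **That one label unmasks others.** Section 7.0 places two active subjects and one placebo subject in each set of three by route and cohort, so a placebo label would in principle identify the other two. That needs an observer who knows the block rule, the cohort membership and each member's route, and it needs sets undisturbed by replacement. It comes from the block size, not from the label.
- **That most safety measures are subjective.** Section 5.1 also lists fever and laboratory values, erythema and induration can be measured, and a severity grading guide is appended. The point concerns part of the safety data.

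What the replies do not answer is that a separate injector hides nothing from the person being injected or from those standing nearby.

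**Conclusion.** The point holds as an avoidable weakness that the protocol's own wording creates. It is not a detail left to another document: section 9.1 specifies a label that shows the assignment, and section 7.0 keeps the assessors close by, with products that can be told apart and no masking of label or barrel described. The size is four opportunities per subject, 72 in all if exactly 18 are dosed. The probability of a sighting at any one injection is unknown.

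A reader might infer that the blind is in fact lost or that the safety results could not be trusted. The documents do not support that. The conclusion assumes only that the procedure is carried out as written and that no unstated masking is in use at the site. The change is a cheap improvement, best made before the first injection because unblinding cannot be undone afterwards.

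**What to change.** **Section 9.1**
- Label each syringe with study ID, dose number, date and expiry time only.
- Keep the assignment in the pharmacy dispensation log, and keep the two-pharmacist check there.
- Have the injector's log record study ID, date, site and side. If a bedside record of product is wanted, keep it sealed and closed to study staff.
- Issue every syringe in an opaque sleeve, which also covers the difference in appearance.

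**Section 7.0**
- State that study staff stay within call during the injection but out of sight of the syringe.

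**Cost.** New wording in two sections, a label template and sleeves. No added subjects, visits or staff. The real downside is that the open bedside record of product is lost or restricted, so checking what was given would rely on the pharmacy log or a sealed record.
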